### 3 Analysis population

#### 3.1 Patient flow description

A patient flow diagram (flow chart) will be created in line with the CONSORT 2010 recommendations. This will contain:

- The number of eligible, randomised patients and the number of patients having actually followed the intervention assigned by randomisation;
- Early withdrawals from the intervention and the reasons, and patients lost to follow-up;
- The number of patients excluded from the analysis.

The number of patients randomised but ineligible, if any, will also be reported as well as the reason for ineligibility.

[figure not shown]

#### 3.2 Analysis populations definition

**Intention-to-treat (ITT):** this population includes all patients randomised into the trial. The patients are analysed in the group to which they were randomised, regardless of the treatment received and regardless of any protocol deviations.

No data will be analysed for patients for whom a signed informed consent form was not collected or for patients who withdrew their consent to use their data during the course of the study. The data concerning these patients, if any have been collected, will be destroyed. The presence of any such patients will be documented in the study flow chart.

### **3.3 Calculation of the required number of subjects**

The calculation of the required number of subjects is detailed in protocol version no. 5.0 dated 07/04/2017.

## **4 Principles of analysis**

### **4.1 General principles for the endpoint analysis**

The results will be reported in line with the CONSORT 2010 recommendations.

The endpoint analysis will be carried out in the ITT population.

The statistical analysis will be carried out with blinding in terms of the randomisation group.

No interim analysis is planned for this trial.

All the endpoints will be tested for superiority.

As the analyses are based on modelling or other numerical approaches, they require verification of the underlying hypotheses as well as convergence of their algorithms. If these conditions are not verified, an alternative method will be used.

The analyses will be carried out using R software version 3.4.4 or later (The R Foundation for Statistical Computing, Vienna, Austria).

The tests used will be bilateral with a significance threshold of 2.5% for the two primary endpoints and 5% for the secondary endpoints. The 2.5% threshold was chosen to take into account the double primary endpoint.

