## **IX.2 - JUSTIFICATION OF THE REQUIRED NUMBER OF SUBJECTS**

The first primary endpoint is the percentage of patients able to be discharged from the surgical department on D4, plus or minus 1 day. The expected percentage in the control arm is 20%. The sample size of 130 patients per arm will allow for an odds ratio of 2.15 (logrank test) with a power of 90% for a p-value of 2.5% in bilateral formulation in order to take into account the double endpoint. The second primary endpoint is the WOMAC function area under the curve analysis at 6 months. The total number of 260 subjects enrolled (130 per group) will allow to demonstrate an effect size of 0.45 for comparison of the average areas under the curve with a power equal to 90% (p-value equal to 2.5%, Mann-Whitney test). Taking into account approximately 10% losses-to-follow-up before the procedure, the number of patients to be enrolled into each study arm will be approximately 150, giving a total of 300.

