### **2. Primary endpoint analysis**

a) The percentage of patients able to be discharged from the surgical department on D4, plus or minus 1 day, will be compared between the 2 groups using the Chi-squared test. Furthermore, analyses adjusted for possible confounding factors (such as patient weight) will also be carried out using a logistic regression model. In addition, an operator effect will be added secondarily to the model to take into account the correlation between the time periods observed in patients operated on by the same surgeon in the event that there is an operator effect present. The results of the adjusted models will be compared to the non-adjusted model.

b) The WOMAC area under the curve between enrolment and 6 months will be calculated using the trapezoidal rule. The mean areas under the curve will be compared using the non-parametric Mann-Whitney test. In the event of missing data after the initial visit, an area under the curve of 1 will be used.

The endpoint tests will be considered significant at the 2.5% threshold so as to take into account the double primary endpoint.

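### Both primary endpoints are tested at a fixed 2.5%; Holm's step-down rule keeps the same 5% family-wise control and gives more power with the same patients

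*Supplement*

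**What the plan says.** SAP v2.0, section 4.1, sets the rule: "The tests used will be bilateral with a significance threshold of 2.5% for the two primary endpoints and 5% for the secondary endpoints". The reason follows: "The 2.5% threshold was chosen to take into account the double primary endpoint". The latest protocol agrees in IX.4, item 2: "The endpoint tests will be considered significant at the 2.5% threshold so as to take into account the double primary endpoint". Its sample-size section (IX.2) uses the same level for the discharge endpoint, "for a p-value of 2.5% in bilateral formulation in order to take into account the double endpoint", and 2.5% again for the WOMAC function area under the curve (AUC).

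Neither document has a step-down, hierarchical or alpha-recycling rule. Nothing else draws on the 5%: "No interim analysis is planned for this trial".

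**The concern.** A fixed 2.5%/2.5% split is plain Bonferroni. Once one null hypothesis has been rejected, the 2.5% spent on it does no further work, and the remaining endpoint is still held to 2.5%. Holm's rule then tests the remaining endpoint at 5% without raising the family-wise error above 5%.

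What is at stake is a result in the gap between 2.5% and 5%. A discharge p-value of 0.03 beside a clearly significant AUC is negative under the present text and positive under Holm, with the same overall error guarantee. The primary objective names both discharge ability and functional recovery, so the chance of showing both is of real interest. The discharge endpoint also appears to have less power than planned, so it has most to gain.

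**Working it through.** **Inputs (protocol IX.2).** 130 patients per arm; two-sided 2.5% per endpoint; discharge ability 20% in controls with odds ratio 2.15; AUC effect size 0.45 by the Mann-Whitney test; 90% power claimed for each. The correlation between the endpoints is not given; 0, 0.3 and 0.6 are assumed.

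**1. The plan's own figures.**
- *Family-wise error:* 0.025 + 0.025 = 0.05 at most; 1 − 0.975² = 0.0494 if independent. The planned control is valid.
- *AUC:* n = 2 × (2.241 + 1.282)² / 0.45² = 123 per arm; divided by the Mann-Whitney efficiency 3/π = 0.955, this is 129. With 130 per arm the power is 90.4%, so the stated figure reproduces. At 5% it would be 94.4%.
- *Discharge:* odds ratio 2.15 on 20% gives 0.43 / 1.23 = 35.0%. The standard error of the difference is 0.0554 pooled and 0.0546 unpooled. Chi-squared power at 2.5% is Φ[(0.1496 − 2.241 × 0.0554) / 0.0546] = 68%, and at 5% it is 77%. The stated 90% does not reproduce.
- *Other readings of 2.15:* the text pairs it with a logrank test. As a hazard ratio it gives 1 − 0.8^2.15 = 38.1%, with power 84% at 2.5% and 90% at 5%. As a risk ratio it gives 43%, with power 96% at 2.5%.

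**2. Holm controls the error.** If both nulls are true, any false rejection needs at least one p-value ≤ 2.5%, which has probability at most 5%. If only one null is true, it is rejected only when its own p-value is ≤ 5%. Neither step uses the correlation.

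**3. The gain, with independent endpoints.** Write P for power at 2.5% and P′ for power at 5%. Holm power for endpoint 1 is P₁ + P₂ × (P′₁ − P₁).
- Discharge at 35.0%: 0.680 + 0.904 × (0.774 − 0.680) = 0.765.
- Discharge at 38.1%: 0.840 + 0.904 × (0.900 − 0.840) = 0.894.
- AUC, with discharge at 35.0%: 0.904 + 0.680 × (0.944 − 0.904) = 0.931.

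**4. The gain, with correlated endpoints.** Simulation of two correlated normal test statistics, 2 million draws per case; power in %, fixed 2.5% → Holm:

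| Case | Corr. | Discharge | AUC | Both | At least one |
|---|---|---|---|---|---|
| 90% each, as planned | 0 | 90.0 → 93.7 | 90.0 → 93.7 | 81.0 → 88.3 | 99.0, same |
| | 0.3 | 90.0 → 93.3 | 90.0 → 93.3 | 82.1 → 88.8 | 97.8, same |
| | 0.6 | 90.0 → 92.9 | 90.0 → 92.9 | 83.9 → 89.7 | 96.1, same |
| Discharge 20% v 35.0% | 0 | 68.0 → 76.5 | 90.4 → 93.1 | 61.5 → 72.6 | 96.9, same |
| | 0.3 | 68.0 → 76.1 | 90.4 → 92.4 | 63.4 → 73.6 | 94.9, same |
| | 0.6 | 68.0 → 76.2 | 90.4 → 91.6 | 65.7 → 75.1 | 92.7, same |

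**5. Simulated error.** With both nulls true, the family-wise error is 4.95%, 4.81% and 4.50% at the three correlations, the same under both rules. With one null true and the other endpoint at 90% power, the true null is rejected 2.5% of the time under the fixed rule and 4.7%, 4.7% and 4.4% under Holm, still below 5%.

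**The case against.** The fixed split is not an error. It is valid, prespecified and the same in the sample size, the protocol analysis and the SAP. That stands in full: this is lost efficiency, and the trial's conclusions would be sound without the change.

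- **Splitting alpha implies that success on either endpoint counts, and Holm does nothing for that.** Correct: its first step is the same 2.5% test. The gain comes only after one endpoint has succeeded, and lies in what can be claimed about the other. Had success been defined as both endpoints together, no split would be needed at all.
- **The 8-point gain on discharge rests on a separate weakness in the sample-size paragraph.** Partly true. The 68% depends on reading 2.15 as an odds ratio, as the text words it. The gain is about 5 points at 38.1% and 3 to 4 points if 90% is taken at face value. Holm narrows the shortfall but does not close it.
- **The powers come from the planning tests.** They use chi-squared and Mann-Whitney, whereas the SAP uses a Poisson GEE and a linear mixed model with imputation. True, so the exact figures may differ. The ordering of the two rules does not, because Holm works on whatever p-values the models give.
- **Intervals become less tidy.** An endpoint declared significant at the second step can have a 97.5% interval that includes no effect. This is a real reporting cost, but a small one: the SAP sets no interval level for the primary endpoints.
- **SAP v2.0 is already validated (29/03/2018), and the protocol would change too.** This bears on timing. If unblinding has occurred, the fixed rule must stand.

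**Conclusion.** The concern holds. For the same patients, data and 5% family-wise error, Holm is never less powerful than the fixed split and is usually more so. The gain is 3 to 4 points per endpoint and 6 to 7 points for both at the planned 90%. If discharge is 20% against 35.0%, it is about 8 points on discharge, 1 to 3 on the AUC and 9 to 11 for both. There is none for at least one endpoint.

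These sizes rest on 130 analysable patients per arm, the planning tests, and assumed correlations of 0 to 0.6. That Holm rejects at least as much, with the same control, depends on none of them. The change is advisable but not essential to the trial's validity.

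**What to change.** Replace the threshold sentences in SAP 4.1, and the matching sentence in protocol IX.4, with:

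> The two primary endpoints are tested by the Holm procedure at a two-sided family-wise 5%: the smaller p-value is compared with 2.5% and, if significant, the larger with 5%. 97.5% confidence intervals are reported for both endpoints.

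Name the single p-value per endpoint that enters the procedure, since SAP 5.1.2 reports both a difference and a ratio for discharge. State in the SAP that a 97.5% interval may include no effect for an endpoint declared significant at the second step.

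The cost is one entry in the SAP change log, dated before unblinding, and handling of the protocol edit under its amendment section (XII.3). No patients, data or models change, and the sample size can stay at 2.5% per endpoint as a conservative basis.

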### **4.2 Baseline patient characteristics**

The baseline patient characteristics collected at enrolment will be described globally and by group in terms of means, standard deviations, medians, interquartile ranges, minimum and maximum for quantitative variables and by their sample sizes and percentages by modality for qualitative variables. The number of missing pieces of data will also be recorded for each variable. No statistical tests comparing the groups will be performed.

### **4.3 Compliance analysis**

Compliance will be described for patients in the intervention group. The number and percentage of patients having taken part in all sessions as well as details of participation per session will be reported. The compliance analysis will be carried out in a second phase, after the primary and secondary endpoint analysis, as it requires unblinding.

### **4.4 Management of missing data**

In the event of missing data regarding the primary endpoints, multivariate imputation by chained equations (MICE) will be carried out.

Imputations will be carried out separately for the patients in the two groups. The baseline characteristics and the primary endpoints (ability at discharge and AUC of the function subscale of the WOMAC index) will be used in the prediction model. Predictive mean matching imputation will be used for the continuous data, logistic regression will be used for the binary data and multinomial regression will be used for the categorical data.

For the MICE procedure, it is common practice to use 10 iterations (Raghunathan TE, Solenberger PW, Van Hoewyk J. IVEware: Imputation and Variance Estimation Software. Ann Arbor, MI: Survey Methodology Program, Survey Research Center, Institute for Social Research, University of Michigan; 2007.

<http://www.isr.umich.edu/src/smp/ive/>). This value will therefore be used. For the number of imputations, it has been suggested as a general rule to use the same number of imputations as the percentage of observations with missing data (White IR *et al.*, Stat Med, 2010, 30: 377-399). This recommendation will be followed with rounding up to the next unit.

Convergence of the multiple imputation algorithm and the imputation results will be verified (van Buuren S & Groothuis-Oudshoorn K, J Stat Soft, 2011, 45: 1-97)

On the other hand, it has been demonstrated that using multiple imputation does not improve the results in mixed models for longitudinal data and that mixed models on imputed data can give unstable results (Twisk J *et al.*, J Clin Epidemiol, 2013, 66 :1022-1028). The secondary endpoints, analysed using longitudinal mixed models, will therefore not be imputed.

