## **VI.2 - SECONDARY ENDPOINTS**

### **Efficacy criteria**

At 6 months and 12 months:

- The average change from baseline in the average knee pain intensity in the past 48 hours, assessed using a self-administered 11-point numeric scale (0 = no pain and 100 = maximum pain)
- The average change from baseline in the average function assessed using the area under the curve of the function subscale of the WOMAC index (0 = best possible function and 100 = worst possible function)
- The average change from baseline in the average quality of life assessed using the physical and psychological components of the MOS SF-12 score (0 = worst possible quality of life and 100 = best possible quality of life) and using the EQ-5D-3L score (1111 = best possible quality of life and 33333 = worst possible quality of life)
- The average change from baseline in the average self-reported number of steps in the past week, measured using a pedometer.
- The average treatment satisfaction assessed using a self-administered 11-point numeric scale (0 = zero satisfaction and 100 = maximum satisfaction).
- The cost-effectiveness assessed using the cost-effectiveness ratio.

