| 10. Getting out of bed                                  |  |  |  |  |  |
| 11. Taking off tights or socks                          |  |  |  |  |  |
| 12. Lying down in bed                                   |  |  |  |  |  |
| 13. Getting in or out of the bath                       |  |  |  |  |  |
| 14. Sitting down                                        |  |  |  |  |  |
| 15. Sitting down on and standing up from the toilet     |  |  |  |  |  |
| 16. Cleaning the house                                  |  |  |  |  |  |
| 17. Carrying out daily housework                        |  |  |  |  |  |

Calculation = (sum/17) x 25

Total 0-100 =

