## **5.2 Speed of functional recovery**

### **5.2.1 Definition**

The second primary endpoint is the speed of postoperative functional recovery at month 6. This is assessed using the area under the curve of the function subscale of the WOMAC index. The area under the curve will be defined by the trapezoidal rule.

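### The WOMAC AUC is imputed as a single number without the patient's own post-enrolment WOMAC scores, and the protocol's conflicting AUC = 1 rule was never withdrawn

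*Supplement*

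**What the plan says.** **SAP, version 2.0.** Section 4.4 states: "In the event of missing data regarding the primary endpoints, multivariate imputation by chained equations (MICE) will be carried out". Imputation is run separately by arm. The predictors are baseline characteristics plus the two endpoints: "the primary endpoints (ability at discharge and AUC of the function subscale of the WOMAC index) will be used in the prediction model". No WOMAC score after enrolment is listed. Section 5.2.1 defines the outcome in one line: "The area under the curve will be defined by the trapezoidal rule". It gives no start point, time unit or rule for a curve with gaps. Section 5.2.2 analyses the AUC with a linear mixed model in each imputed dataset and pools by Rubin's Rules. Section 5.2.3 offers two sensitivity analyses, one unadjusted and one without imputation.

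**Protocol, latest version.** Section IX.4, item 2 b) sets the window: "The WOMAC area under the curve between enrolment and 6 months will be calculated using the trapezoidal rule". It then adds: "In the event of missing data after the initial visit, an area under the curve of 1 will be used". Section VI.2 gives the direction of the scale, "0 = best possible function and 100 = worst possible function", and Annex 3 gives the scoring, "Calculation = (sum/17) x 25", which yields 0 to 100.

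**Collection.** Protocol VII.1 and VII.3 collect WOMAC function at enrolment, before surgery, at 6 weeks and at months 3, 4, 5 and 6. That is seven points, six of them after enrolment. The 6-week, month 4, month 5 and month 6 contacts are by post or email, and month 3 may be.

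**The concern.** The AUC is built from seven scores, and a patient with an incomplete curve will usually have supplied several of them. Those scores are the best available predictors of the missing part, and the stated model omits them. Two patients with the same baseline and discharge ability get draws from the same distribution even if one was recovering well at month 3 and the other badly.

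This wastes information. It also means that dropout driven by observed recovery is not accounted for beyond what baseline and discharge ability explain. Neither sensitivity analysis uses partial curves. By contrast, SAP 6.2.2 analyses the secondary personalised WOMAC with a longitudinal mixed model over every visit, so partial follow-up does contribute there.

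The protocol's AUC = 1 rule raises a separate problem. Two documents give two different answers for the same missing co-primary outcome.

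**Working it through.** **1. The plan's own figure.** Protocol IX.2 gives effect size 0.45, 90% power, two-sided 2.5%, Mann-Whitney, 130 per arm.
- n = 2 × (2.241 + 1.282)² / 0.45² = 122.6 for a comparison of means, so 123.
- Dividing by the Mann-Whitney efficiency 3/π: 122.6 / 0.955 = 128.4, so 129. Power at 130 is 90.4%. The figure reproduces.
- The allowance of about 10% covers losses before surgery: 130 / 0.9 = 144.4, so 145, against about 150 planned. Nothing is allowed for missed questionnaires afterwards.

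**2. How many curves are incomplete.** The documents give no missed-questionnaire rate, so these are assumptions.
- Independent misses at each of six visits: 1 − 0.95⁶ = 26%; 1 − 0.90⁶ = 47%.
- Clustered misses (beta-binomial, within-patient correlation 0.2 to 0.4): 14-18% at 5% per visit, 26-34% at 10%.
- If interior gaps are interpolated, only a missing month 6 leaves the curve open: 5-10%.

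**3. Precision.** Simulation with 150 per arm, seven visits, 10% lost before surgery, independent misses, and any miss making the AUC missing. Assumed: visit SD 18, a within-patient correlation and a mean profile. The AUC is time-averaged with SD 15.37, so the true difference is 0.45 × 15.37 = 6.92 points. There were 60 runs per scenario and 8 imputations, using Bayesian linear regression by arm instead of predictive mean matching, with discharge ability left out.

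| Misses per visit | AUCs incomplete | SE, AUC-level | SE, visit-level | SE, complete data | Variance ratio, AUC-level to visit-level |
|---|---|---|---|---|---|
| 5% | 34.5% | 1.93 | 1.79 | 1.77 | (1.93/1.79)² = 1.16 |
| 10% | 52.5% | 2.14 | 1.81 | 1.78 | (2.14/1.81)² = 1.40 |

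These are mean estimated SEs. As a ceiling, if baseline predicted nothing the ratio would be about 1/(1 − 0.265) = 1.36 at 5% and 1/(1 − 0.469) = 1.88 at 10%. Both results lie below it. Power figures from 60 runs carry 4 to 6 points of error, so I do not rely on them.

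**4. Bias when dropout after month 3 depends on the month 3 score.**
- *Separate simulation* (200-300 trials per setting, 28-31% incomplete, AUC SD 85 point-months, true difference about 37). AUC-level imputation from enrolment WOMAC gives 34.8 when the mechanism is the same in both arms and 26.7 when it is stronger in control. Visit-level maximum likelihood gives 37.3-37.4. The complete-data SE is 85 × √(2/150) = 9.8, so the shortfalls are (37 − 34.8)/9.8 = 0.2 SE and (37 − 26.7)/9.8 = 1.1 SE.
- *Deliberately adverse case* (set-up of step 3, dropout in opposite directions by arm). AUC-level gives −3.9 (31% incomplete) and −3.5 (40%); visit-level −6.3 and −6.7; complete data in the same trials −6.4 and −6.8.

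**5. What AUC = 1 would mean.** Follow-up of 14-15 months less 12 after surgery puts enrolment 2-3 months before it, so the protocol's window is 8-9 months.
- The maximum area is 800-900 score-months, and 1 is 0.11-0.13% of it. Over 6 months it is 1/600 = 0.17%; time-averaged, 1%.
- If the rule were applied, with an assumed mean of 30 and SD 15, 10% missing per arm takes the effect size from 0.45 to 0.375 (power 84% at 150 per arm).
- With no true effect, a 5-point imbalance in missingness creates 0.05 × (30 − 1) = 1.45 points in favour of the arm with more missing data.

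**The case against.** **The AUC = 1 rule is not what will be done.** This stands. Protocol IX.1 leaves the detail to a SAP prepared before database freeze. The SAP is later, prescribes MICE, and also replaces the protocol's chi-squared and Mann-Whitney tests. A reader might infer that both rules distort the primary result, but they are alternatives. The effects in step 5 describe a rule that the SAP does not use. What remains is that the SAP neither mentions nor withdraws it: the SAP says it was written from protocol 5.0, and its change log records only an EQ-5D correction.

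**The unit of the AUC is undefined.** Also fair. Rescaled to 0-1, a value of 1 would be worst; expressed relative to baseline, it would mean no change. Neither rescaling is documented, and the only scale given runs from 0 (best) to 100 (worst).

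**Nothing says that one missed questionnaire voids the AUC.** True. A trapezoid can bridge an interior gap, and then the other scores are used. A reader might take 26-47% without an AUC as what the plan implies, but that needs both the strict rule and independent misses. Protocol VII.5 also provides telephone and email reminders and data collection by telephone. Silence on the point is still a gap, and interpolation cannot supply a missing month 6.

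**The model is not baseline-only.** Correct: discharge ability is a post-surgical measure and is included. It is one early in-hospital assessment and cannot stand in for scores from 6 weeks onwards. Because the simulations omit it, they may somewhat overstate the loss.

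**Conclusion.** The point holds in two parts.

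First, the stated imputation model leaves out the patient's observed post-enrolment function scores whenever an AUC is imputed. The variance penalty is about 1.16-1.40 under step 3's assumptions, and smaller if misses cluster or interior gaps are interpolated. Bias under recovery-dependent dropout is slight when the mechanism is the same in both arms (about 0.2 SE). A reader might infer serious bias in general. The documents do not support that: the large figures need dropout that differs by arm, and nothing in the plan predicts it. The sizes rest on assumed missingness, correlation and mean profile. The direction of the precision loss does not.

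Second, the protocol and SAP give conflicting rules for the same missing outcome. On the documented scale, the protocol's rule would count missing patients as near-perfect recoveries. This is an unreconciled conflict and does not add to the first part.

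**What to change.** In SAP 4.4, keep MICE by arm but impute the WOMAC function score at each visit, with the other visit scores, baseline characteristics and discharge ability as predictors. Compute the AUC in each completed dataset, fit the model of SAP 5.2.2, and pool by Rubin's Rules. Keep the predictor list to these: with about 150 patients per arm, adding every daily test level from D1 to D5, length of stay and discharge destination risks collinearity and unstable imputations.

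In SAP 5.2.1, state the AUC's start and end points and its unit, and confirm that gaps are filled by the imputation. In protocol IX.4, item 2 b), delete the AUC = 1 sentence, or record in the SAP that it is superseded.

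The cost is wording in two documents and slightly longer imputation code. No new data are needed. The change should be made before unblinding.

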#### **5.1.2 Primary analysis**

The proportion of patients who are independent at the time of discharge from the surgical department in each of the arms, the difference between these proportions and their ratio (rate ratio) will be estimated as well as their standard errors. The estimation of the difference in the rate of independence and the rate ratio will be adjusted to the centre. The adjusted analysis of the rate ratio will use a GEE Poisson model with an exchangeable correlation structure assuming a correlation for patients operated on by the same surgeon. The centre will be used as a fixed effect. The adjusted difference in proportions will be derived from the model used for the rate ratio. The analyses will be carried out on each of the imputed databases then pooled according to Rubin's Rules.

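### The imputation rule in SAP 4.4 leaves seed-to-seed noise of about 0.1 in the primary z-statistics, so a result close to the 2.5% threshold may not be reproducible

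*Supplement*

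**What the plan says.** The latest SAP (section 4.4) imputes missing primary endpoints by chained equations with 10 iterations. "Imputations will be carried out separately for the patients in the two groups." For the number of imputations, m, it cites a general rule to "use the same number of imputations as the percentage of observations with missing data" and adds: "This recommendation will be followed with rounding up to the next unit." So 5% missing gives m = 5, 10% gives m = 10 and 20% gives m = 20. Convergence and the imputed values are to be checked. Section 4.4 states no lower limit for m, no random seed, no Monte Carlo error criterion, and no provision for raising m when a result is close.

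The imputed analysis is the primary one for both endpoints. Section 5.1.2 says "The analyses will be carried out on each of the imputed databases then pooled according to Rubin's Rules", and section 5.2.2 says the same for the WOMAC area under the curve (AUC). Section 4.1 makes the tests "bilateral with a significance threshold of 2.5% for the two primary endpoints". Analyses without imputation appear only as sensitivity analyses (5.1.3 and 5.2.3). The only loss figure in the documents is about 10% before the procedure (protocol IX.2).

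**The concern.** A pooled estimate from a finite number of imputations is itself random: running the same program on the same data with another seed gives another z and another p. How much it moves depends on m relative to the missing information. A rule that lets m grow only in proportion to the missing percentage holds this noise roughly constant and never drives it down. That may be good enough for description. Here two primary decisions are read against a sharp threshold, so two analysts who both follow the SAP to the letter could report opposite conclusions when the result is close. A prespecified analysis is meant to exclude that.

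**Working it through.** **Inputs from the documents.** m = 100 × missing fraction f, rounded up (SAP 4.4). Two-sided 2.5% per primary endpoint (SAP 4.1), so the critical z is 2.2414. From protocol IX.2: 130 per arm; for the first endpoint a control rate of 20% and an "odds ratio of 2.15 (logrank test) with a power of 90% for a p-value of 2.5% in bilateral formulation"; for the AUC an effect size of 0.45 with 90% power. Enrolment is 150 per arm.

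**Assumption.** The fraction of missing information (FMI) is not given. I take FMI = f as the base case and let it fall to 0.5 f, with f from 3% to 40%.

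**The plan's own figures.** The documents state none for Monte Carlo error. As a check on reading alpha and power, the AUC sample size does reproduce: 123 per group for a comparison of means, divided by the Mann-Whitney efficiency 3/π = 0.955, gives 129, against 130 stated.

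**Step 1: noise in the pooled estimate.** The Monte Carlo variance is B/m, where B is the between-imputation variance. In units of the pooled standard error, the SD is about √(FMI/m). With m = 100 f and FMI = f this is √(f/(100 f)) = √0.01 = 0.10 at every missing rate.

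**Step 2: noise in the pooled standard error.** This adds about (z/2) × FMI × √(2/(m − 1)). At 10% missing and m = 10: 1.1207 × 0.10 × √(2/9) = 0.053, so the total is √(0.10² + 0.053²) = 0.113. The totals:

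| Missing | m | FMI = f | FMI = 0.5 f |
|---|---|---|---|
| 5% | 5 | 0.108 | 0.073 |
| 10% | 10 | 0.113 | 0.075 |
| 20% | 20 | 0.124 | 0.080 |
| 30% | 30 | 0.133 | 0.083 |
| 40% | 40 | 0.142 | 0.087 |

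**Step 3: simulation.** Fixed data sets (150 per arm, imputation by arm, Rubin's rules) were re-imputed under many seeds, with z near the threshold. For the AUC, the SD of the statistic across seeds was 0.112, 0.119, 0.126 and 0.137 at 5, 10, 20 and 30% missing with no useful covariate, and 0.094, 0.098, 0.111 and 0.117 with a covariate correlated 0.5. For the binary endpoint it was 0.102, 0.110, 0.121 and 0.128. These runs left out centre and surgeon terms, and used normal-regression and Beta-binomial draws in place of predictive mean matching and logistic regression.

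**Step 4: what it does to p.** At z = 2.2414, a shift of ±0.1 moves p between 0.019 and 0.032, and ±0.2 between 0.015 and 0.041. Two SDs either side of the threshold is the band z = 2.04 to 2.44. For a result at p = 0.02 (z = 2.326), on a normal reference:
- SD 0.10: 2.326 ± 1.96 × 0.10 = 2.130 to 2.522, so p = 0.033 to 0.012.
- SD 0.126: 2.326 ± 0.247 = 2.079 to 2.573, so p = 0.038 to 0.010.

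In one simulated binary data set with 10% missing and m = 10 (27/135 against 43/135 observed), p ran from 0.019 to 0.047 (5th to 95th percentile over seeds), and 27% of seeds gave p below 0.025.

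**Step 5: how often two seeds disagree.** With noise SD s, the probability is approximately φ(distance of the expected z from 2.2414) × (2/√π) × s, where φ is the standard normal density. At s = 0.10:
- 90% power: φ(1.28) = 0.1755, and 0.1755 × 1.128 × 0.10 = 2.0%.
- 68% power: φ(0.47) = 0.358, giving 4.0%.
- 50% power: φ(0) = 0.399, giving 4.5%.
- No effect (both tails): 2 × 0.0324 × 1.128 × 0.10 = 0.7%.

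The 68% is the power of a two-sided 2.5% comparison of 20% with 35% (odds ratio 2.15) at 130 per arm. Protocol IX.2 states 90%. That difference is a separate matter, and the present point does not depend on it.

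**The case against.** The rule is prespecified, published and cited, and the pooled test is valid. Rubin's rules carry the finite number of imputations through the factor (1 + 1/m) and the t reference. A reader might infer bias or an inflated type I error, and nothing in the documents supports that. Nor do they support the broader reading that the trial's conclusion generally hangs on the seed: at the stated 90% power the two-seed disagreement is about 1 trial in 50 per endpoint.

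The size of the noise also depends on things left open. Section 4.4 does not say whether the percentage is taken per endpoint or over patients incomplete on either. If it is joint, the more complete endpoint gets more imputations than its own missing rate implies: 10% missing with m = 30 gives √(0.10/30) = 0.058, or about 0.065 with noise in the standard error. Good predictors lower it too (0.073 to 0.083 at half the missing fraction for 5 to 30% missing). The planned analyses without imputation need no seed, and the group-blinded analysis limits any choice of seed by its direction. These points reduce the consequences and the severity, but none of them removes the noise.

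A reader might also infer that centre is missing from the imputation model although both analysis models contain it. The text does not show that. Section 4.4 includes baseline characteristics without listing them, and centre, the stratification factor, is known at enrolment.

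Finally, no particular m is uniquely right. An SD of 0.03 from the estimate alone needs m of about 56, 112, 223 or 334 at 5, 10, 20 or 30% missing. A seed alone makes a run repeatable without making it less noisy. That is why the remedy has more than one part.

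**Conclusion.** The point holds and is minor. Under the rule in SAP 4.4 the primary z-statistics carry a seed-to-seed SD of about 0.1, assuming that the fraction of missing information is near the endpoint's missing fraction and that m is set from that endpoint; the plausible range is about 0.06 to 0.14. Results with z between roughly 2.04 and 2.44 are exposed, and outside that band the seed will rarely change the conclusion. This is a weakness in reproducibility at a sharp threshold, in an otherwise valid test. It deserves correction because the remedy costs so little, not because the expected harm is large.

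**What to change.** In SAP 4.4, replace the percentage rule with a fixed, large number of imputations for both primary endpoints, for example m = 200. Prespecify and record the random seed, and report the Monte Carlo standard error of each pooled estimate. At m = 200 the simulated SD of z was 0.013 to 0.058 over 5 to 30% missing, and 0.024 at 10%. At 0.024 the two-seed disagreement at 90% power falls to about 0.1755 × 1.128 × 0.024 = 0.5%. Some noise remains when much is missing, and the reported Monte Carlo error would show it. A fixed m also ends the question of which missing percentage to use. The cost is a short change of text and minutes of computing for 300 patients. Data collection, the endpoints and the analysis models stay as they are.
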